#### OPC-CA

The OPC-CA (Graham & Ziviani, 2021a) is a 13-item measure providing a broad indication of the implementation of OPC, from case-note records. Items capture key elements of OPC including goal-oriented conversation, analysis, action planning, evaluation, and generalization. Relational elements of OPC, such as the use of empathy to engender client trust, are not included given these are unlikely to be documented.

The OPC-CA will be conducted on two occasions: first, prior to therapist randomization, with a retrospective sample of three case note entries for each of three dyads (closed cases), who meet the study criteria; second, at T16 with three case note entries selected for each dyad who participated in the study. For the OPC group, this will allow monitoring of adherence to OPC; for the Usual Care group, this will help to determine the continuity of usual care and any contamination of the Usual Care group.

### Qualitative Measure

A post-intervention semi-structured interview will explore Māori caregiver experiences (*n *= 10) of engaging in OPC, in the context of their cultural expectations of health professionals. Interview questions will be guided Kaupapa Māori principles (Smith, 2013). Interviews will be conducted by a Māori research fellow with adherence to culturally informed processes of engagement (Pitama et al., 2017).

## Statistical Methods

Participant data will be analyzed as-randomized (intention-to-treat, ITT). Two-sided *P* values will be reported and an alpha of 0.05 used for the construction of confidence intervals and for determining statistical significance. The analysis will be performed using R specialist statistical software (R Core Team, 2021). A detailed statistical analysis plan (SAP) will be prepared by the study biostatistician and agreed upon by the PI prior to any analysis of the data.

Differences between groups in outcome measures (COPM scores, DASS-21, and PEDI-CAT scores at 16 weeks) will be estimated with 95% confidence intervals using a “constrained baseline analysis” where a linear mixed-effects model is fitted to the individual level data with time and treatment included as fixed effects. Correlations within the data will be accounted for by incorporating the following random effects; cluster, an individual within cluster, and time within cluster, and a Kenward–Roger correction will be applied due to the small number of clusters (Hooper et al., 2018). Psychometric analysis of therapist self-completed and researcher-completed OPC-FM scores will be conducted to assess the validity and reliability of this instrument. Researcher completed OPC-FM scores, Session Characteristics, and SRSs will be summarised first by a therapist, and then by the treatment group. Linear regression analysis adjusting for clustering will be used to estimate mean treatment group differences with 95% confidence intervals.

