## Method

### Trial Design

This trial (entitled the MANA study: Meaning, Agency and Nurturing Autonomy through OPC) will examine if OPC is superior to usual care using a single-blind, 2-arm parallel group, cluster RCT design, with 1:1 allocation. Clustering will take place at the level of the therapist. See Figure 1 for a flowchart of the MANA study and Supplemental Additional File 1 for the full protocol which has been compiled following the SPIRIT (Standard Protocol Items: Recommendations for Interventional Trials) guidelines (Chan et al., 2013).

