#### Study Setting and Recruitment

All participants will be recruited from publicly funded Aotearoa/New Zealand community-based rehabilitation services that provide rehabilitation services to children with ND and their families. Each service operates independently, with varying workplace cultures and service processes. Consultations are delivered either in-person or via tele-health.

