### Randomization Process

Therapists represent clusters in the study design with study participants defined as caregivers and their children with ND (dyads). After completion of a retrospective case note audit, therapists (N ≥ 14) will be randomized into the OPC or Usual Care groups via a computer-generated randomization sequence, stratified by service (Harris et al., 2009). Thus, services with multiple therapists enlisted in the study will have a mixture of control and intervention group therapists. Therapists in both groups will then each recruit child–caregiver dyads to the study from successive eligible referrals to the service until the total sample size (N = 84) is reached. To enable adequate recruitment of Māori dyads for equal explanatory power for ethnicity, therapists will continue to invite Māori to participate until 42 Māori dyads are recruited (potentially increasing the total sample size to N = 126), or data collection has ended.

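### Therapists are randomised within service, but neither listed model contains service: intervals are too wide if services differ in 16-week outcome given baseline, while the effect on power cannot be fixed from the article

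*Protocol article*

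**What the plan says.** Under Trial Design, "Clustering will take place at the level of the therapist". Under Randomization Process, therapists "will be randomized into the OPC or Usual Care groups via a computer-generated randomization sequence, stratified by service", and as a result "services with multiple therapists enlisted in the study will have a mixture of control and intervention group therapists". Study Setting and Recruitment describes the services: "Each service operates independently, with varying workplace cultures and service processes".

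Under Statistical Methods, "a linear mixed-effects model is fitted to the individual level data with time and treatment included as fixed effects". The random effects are "cluster, an individual within cluster, and time within cluster", and "a Kenward–Roger correction will be applied due to the small number of clusters". This one model serves COPM, DASS-21 and PEDI-CAT scores at 16 weeks, as a constrained baseline analysis.

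Under Additional Analyzes, the adjusted model adds therapist profession and experience, socio-economic status, caregiver ethnicity, education and DASS-21, child age and child ND. Service appears in neither list, and no other section adds it to a model.

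**The concern.** Randomising within service balances services across the arms, so service differences largely cancel from the treatment comparison. A model that does not know about service still sees therapists in different services differing from one another, and it counts that spread as therapist-level noise. The reported standard error then exceeds the true one, the interval covers more than 95% of the time, and the precision gained by stratifying is not used.

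With about 14 therapists, therapist-level variance largely determines the precision of the trial, so this is worth settling. Because the article spells out the terms of both models, this is a stated specification and not a detail simply left to the SAP.

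**Working it through.** **1. The plan's own sample size.** Inputs from Sample Size: difference 2, SD 2, two-sided alpha 0.05, power 90%. The noncentral t gives 89.97% power at 44 dyads and 91.2% at 46, so 46 reproduces. Inflation: 46 × 1.2 / 0.80 / 0.85 = 81.2, rounded up to 14 × 6 = 84, which also reproduces. The design effect implies 1.2 = 1 + (6 − 1) × ICC, so ICC = 0.04.

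**2. Standard error with and without service.** Planning values: total variance 2² = 4; dyads analysed per therapist 6 × 0.85 = 5.1; therapist share 4%. Assumed, because the article gives neither: 7 services of two therapists and a service share of 10%. This first step ignores baseline.

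- Service variance 0.10 × 4 = 0.40; therapist variance 0.04 × 4 = 0.16; residual 0.86 × 4 / 5.1 = 0.674.
- True SE of the contrast (service cancels within pairs): √(2 × (0.16 + 0.674) / 7) = 0.488.
- SE reported without service: √(2 × (0.40 + 0.16 + 0.674) / 7) = 0.594. Simulation gives 0.595.

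The simulated 95% interval without service covers 97.7%, that is, a type I error of about 2.3%. For 4 and 2 services coverage is 97.4% and 96.5%. At a 20% share with 7 services it is 98.9%.

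**3. After baseline adjustment.** The planned analysis uses baseline, so only service variation not already visible at baseline matters. Step 2 was therefore repeated with baseline-adjusted therapist means: 7 pairs, 6 dyads each, effect 2 × (1 − 0.20) = 1.6, and an assumed non-service baseline-to-follow-up correlation of 0.5. Power without service versus with fixed service effects:

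| Service variance carried over from baseline | Share 10% | Share 20% |
|---|---|---|
| All | 93% vs 84% | 93% vs 86% |
| 80% | 90% vs 84% | 87% vs 85% |
| Half | 86% vs 84% | 79% vs 86% |
| None | 80% vs 84% | 67% vs 86% |

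With 5.1 dyads per therapist, the last cell's loss is about 17 points instead of 19, and at a 10% share with no carry-over power goes from 77% to 80%. Type I error without service at the 10% share is about 2% with no carry-over, 3.4% at 80% carry-over and 4.6% at full carry-over; with service it is about 5%. With 4 or 2 larger services and a 10% share, adding service gains about 1 to 8 points while carry-over is incomplete.

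**4. If services do not differ.** With 7 pairs, fixed service effects cut the residual degrees of freedom from 12 to 6 before baseline adjustment. The cost in power is about 7 to 8 points unadjusted (83% to 75% with 5.1 dyads) and about 12 points after baseline adjustment.

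**5. Random service effects.** An idealised version, without baseline adjustment and with 7 pairs and 6 dyads each (within-service SE when the estimated service variance is positive, pooled SE otherwise), gave:

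| Service share | Power, omitted | Power, fixed | Power, random | Type I error, random |
|---|---|---|---|---|
| 0 | 86.7% | 79.5% | 87.9% | 6.9% |
| 5% | 82.1% | 81.1% | 86.3% | 5.7% |
| 10% | 77.5% | 83.1% | 86.3% | 5.4% |
| 20% | 66.7% | 86.1% | 87.5% | 5.3% |

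None of these runs fits the full Kenward–Roger mixed model.

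**The case against.** A reader might infer from the unadjusted figures that leaving service out costs the trial some 5 to 20 points of power. The documents do not support that, for three reasons.

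- The planned analysis adjusts for baseline. Stable service differences are largely absorbed, and in the 7-pair layout the loss shrinks or reverses once enough of the service variance is present at baseline. The article says that services vary in culture and process; it does not say that outcome at 16 weeks given baseline varies by service.
- The shares of 10% and 20% come on top of a 4% therapist share, whereas the design effect implies 4% in total. If all clustering is kept within 4%, adding fixed service effects changes unadjusted power by only about −5 to +2 points.
- The obvious repair has its own price: fixed effects lose degrees of freedom with small services, and random effects may be mildly anticonservative when service variance is near zero.

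It can also be said that the article condenses a fuller protocol and that an SAP will follow. That is a partial defence only, since the terms of both models are listed.

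All three limits on the size stand. What remains is that the analysis ignores the factor by which the trial randomises, and that its intervals are too wide to the extent that services differ given baseline. Neither bias nor an inflated type I error follows from the omission.

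**Conclusion.** The point holds in a limited form. Service is the stratification factor and is absent from both listed models. The consequence is conservatism: type I error of about 2–4% in place of 5% over most of the assumed range, near 1% in the most extreme setting (share 20%, no carry-over), and close to nominal if baseline carries all service differences. The treatment estimate is unbiased.

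The power consequence cannot be fixed from the article. Under the assumptions shown, it runs from a loss of about 17 points (service share 20%, no carry-over, 5.1 dyads per therapist) to none, and a poorly chosen fixed-effects repair can do harm. The figures rest on an assumed number of services, assumed service variances, an assumed baseline correlation and therapist-level approximations. This is a cheap change that should be made, not a threat to the validity of the trial.

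**What to change.** Before 16-week data are collected, which is when the article says the SAP and code will be ready, state how service enters the primary, secondary and adjusted models. The practical form is a random service effect plus a random service-by-time effect, so that service acts on the 16-week contrast. If services turn out few and large, fixed effects with small services pooled are an alternative. Either way, keep services with a single therapist in the analysis and say in advance what happens if a service variance is estimated at zero.

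The cost is a line or two in the model specification, plus extra variance components or lost degrees of freedom. Random effects may be mildly anticonservative when services hardly differ (about 6–7% in the approximate simulations). So simulate the type I error of the chosen Kenward–Roger model with the actual number of services and therapists before locking the SAP. If the sponsor prefers to leave service out, the SAP should say so and give the reason.

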### Additional Analyzes

Baseline therapist and dyad characteristics will be summarised for the whole ITT population using means (standard deviations), medians (interquartile ranges), and frequencies (percentages) as appropriate. Summaries will be tabulated by the treatment group but no hypothesis testing will be undertaken. Goals documented by therapists and identified in the OPC-CA for both intervention and control groups will be compared against goal criteria for OPC and reported descriptively (i.e., counts, percent) (Graham & Ziviani, 2021a).

Adjusted analysis of primary and secondary outcome measures (COPM, PEDI-cat, and DASS-21) will be undertaken by adjusting for the following baseline variables as fixed effects in the model; therapist profession (OT, PT, and SLT), therapist years of experience, caregiver–child socio-economic status, caregiver ethnicity (Māori vs. non-Māori), caregiver education level, caregiver DASS-21, child age, and child ND.

A sensitivity analysis will be conducted on the primary outcome using the as-treated population. Caregiver–child dyads will have been deemed to have received the intervention (OPC) if more than half (two out of the three) OPC-FM assessments (researcher-completed or bias-adjusted therapist self-completed) for the caregiver–child dyad score 80% or above.

The heterogeneity of treatment effects will be assessed using the framework presented by Kent et al., 2010. An outcome prediction score will be calculated for each participant using a multivariable linear regression model including selected baseline variables (excluding the treatment group). A second linear regression model will be fitted including the outcome prediction scores, treatment group, and interaction between the two as independent variables, and observed outcome scores as the dependent variable. In addition, subgroup analysis of Māori caregiver–child dyads is planned a priori. Where interaction effects are found, treatment effects with 95% CI will be presented by each subgroup in tabular form, with continuous predictors dichotomized into approximately equal-sized groups.

Interview data with Māori caregivers will be analyzed by senior Māori researchers using reflexive thematic analysis (Braun & Clarke, 2022). This analysis will be underpinned by Kaupapa Māori Research principles (Smith, 2013) that privilege the perspectives of Māori participants and ensure the interpretation of data is culturally appropriate (Jones et al., 2010).

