#### Depression Anxiety Stress Scales (DASS-21)

Caregiver mental health will be measured using the short form of the DASS-21 (Crawford & Henry, 2003). Parental mental health is an important consideration in family centred intervention for children with neurodisabilities. Prior research on OPC indicates that parental psychological state may be both a mechanism (Graham et al., 2010) and an outcome of OPC (Chien et al., 2020; Graham et al., 2013) hence DASS21 will be collected pre and post-intervention. The DASS21 is a self-report questionnaire with 21 items using a 4-point response scale to measure negative emotional states over the prior week. The DASS-21 has been shown to demonstrate acceptable to excellent internal consistency and concurrent validity (Antony et al., 1998), is widely used with caregivers of clinical paediatric populations (Poole et al., 2018; Rayan & Ahmad, 2017) and is sensitive to change following OPC (Graham et al., 2013).

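### In the adjusted DASS-21 analysis, baseline DASS-21 is both a response value and a covariate, so the standard error is too small and the test is anti-conservative

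*Protocol article*

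**What the plan says.** Statistical Methods sets one model for three outcomes: "Differences between groups in outcome measures (COPM scores, DASS-21, and PEDI-CAT scores at 16 weeks) will be estimated" by a constrained baseline analysis, "where a linear mixed-effects model is fitted to the individual level data with time and treatment included as fixed effects". The random effects are "cluster, an individual within cluster, and time within cluster, and a Kenward–Roger correction will be applied". The DASS-21 section gives two measurements per caregiver: "hence DASS21 will be collected pre and post-intervention".

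Additional Analyzes then states: "Adjusted analysis of primary and secondary outcome measures (COPM, PEDI-cat, and DASS-21) will be undertaken by adjusting for the following baseline variables", entered as fixed effects in the model. The list that follows contains "caregiver education level, caregiver DASS-21, child age, and child ND". DASS-21 is thus named as an outcome and as a covariate in the same sentence, and nothing sets the covariate aside for its own outcome.

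**The concern.** In a constrained baseline analysis the baseline measurement is a response row, tied to the follow-up row through the individual random effect. That is how the model uses baseline information. With two time points, half of the planned DASS-21 responses are baseline values.

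If baseline DASS-21 is also a fixed-effect covariate, those rows are regressed on themselves. Their residuals become artificially small and are pooled with the 16-week residuals, because the stated random effects leave a single individual-level residual variance for both times. The treatment contrast depends on the 16-week rows, so its standard error is understated.

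At stake is the adjusted result for caregiver mental health, which is one of the three lettered secondary hypotheses. Its confidence interval would be too narrow, and it could look more convincing than the unadjusted result for no real reason.

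**Working it through.** **Inputs from the protocol.** Two-sided alpha 0.05 ("Two-sided *P* values will be reported and an alpha of 0.05 used"); the model and correction quoted above; two DASS-21 time points; 84 dyads over 14 therapists, so 6 each; design effect 1.2.

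**The plan's own figures.** It gives no standard error or error rate for this model; the benchmark is the nominal 5%. The sample size used below is reproducible. A two-sample t calculation with difference 2, SD 2 and 90% power gives 23 per arm, or 46 dyads. Then 46 × 1.2 / 0.8 / 0.85 = 81.2, and 14 × 6 = 84.

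**Assumed, because the documents do not give them.** Pre-post correlation ρ; ICC (if 1.2 = 1 + (6 − 1) × ICC, then ICC = 0.04, borrowed from the COPM calculation); cluster autocorrelation; equal variances at both times; the same DASS-21 score as outcome and covariate. Other covariates and missing data are left out.

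**Closed form** (variance 1 at each time, no clustering, large sample, y0 = baseline, y1 = 16 weeks):

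1. The slope of y0 on itself is 1 and that of y1 on y0 is ρ. Pooled, the slope is (1 + ρ)/2.
2. The baseline residual is y0(1 − ρ)/2, with variance (1 − ρ)²/4.
3. The 16-week residual is (y1 − ρy0) − y0(1 − ρ)/2, with variance (1 − ρ²) + (1 − ρ)²/4. This is the true variance factor T for the treatment contrast.
4. The covariance of the two residuals is −(1 − ρ)²/4. It is negative, so the estimated individual variance falls to zero.
5. The model uses the average of the two variances: M = (1 − ρ²)/2 + (1 − ρ)²/4.
6. SE ratio = √(M/T); type I error = 2[1 − Φ(1.96 × ratio)].

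| ρ | T | M | SE ratio | SE too small by | Type I error |
|---|---|---|---|---|---|
| 0.1 | 0.99 + 0.2025 = 1.1925 | 0.495 + 0.2025 = 0.6975 | 0.765 | 23% | 13% |
| 0.5 | 0.75 + 0.0625 = 0.8125 | 0.375 + 0.0625 = 0.4375 | 0.734 | 27% | 15% |
| 0.9 | 0.19 + 0.0025 = 0.1925 | 0.095 + 0.0025 = 0.0975 | 0.712 | 29% | 16% |

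**Simulation of the stated model** (14 clusters × 6 dyads × 2 times, no treatment effect, REML, random effects for cluster, individual and cluster-by-time):

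| Setting | SE / empirical SD | Type I error |
|---|---|---|
| With covariate, z test, ρ 0.3–0.7, ICC 0–0.1, 2,500 runs each | 0.73–0.78 | 13–17% |
| With covariate, exact Kenward-Roger, ρ 0.5–0.7, ICC 0.04, 450–700 runs each | 0.75–0.84 | 11–12% |
| Without covariate, approximate small-sample correction, same settings as first row | 1.01–1.06 | 4–5% |
| Without covariate, exact Kenward-Roger, ρ 0.5, ICC 0.04, 700 runs | 1.09 | 2.6% |

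Monte Carlo error on the 11–12% figures is about 1.2 to 1.5 percentage points. Kenward-Roger reduces the problem but does not remove it. The excess goes when the covariate is dropped.

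**The case against.** **The adjusted analysis might be an ANCOVA.** The Sample Size section speaks of ANCOVA, and the primary outcome section describes adjusting for values at recruitment. In an ANCOVA of the 16-week score, baseline DASS-21 is the right covariate; simulated type I error is then 2.4%. But the first reference concerns only the sample size and the second only COPM. The analysis text names a constrained baseline mixed model for DASS-21 and adds the covariates to the model. The ANCOVA reading is possible but is not what is written.

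**The full protocol or SAP may make the exception.** It may; neither is shown. But this is not an omission left to the SAP. The article states which covariates apply to which outcomes, and an SAP that followed it would carry the problem over.

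**The score may differ on the two sides.** The protocol does not say whether DASS-21 enters as a total or as subscales. The exact self-prediction, and so the figures above, need the same score as outcome and covariate. This limits the figures, not the need for the exception.

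**The affected analysis is supplementary.** This stands and limits the importance. The unadjusted DASS-21 model does not contain the covariate and remains a valid test of the hypothesis.

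**Conclusion.** The point holds for the adjusted DASS-21 analysis as written. The standard error is about 23 to 29% too small and type I error about 13 to 16% with no clustering and no Kenward-Roger correction (correlation 0.1 to 0.9). With clustering and Kenward-Roger they are about 16 to 25% and 11 to 12% (correlation 0.5 to 0.7, ICC 0.04). All correlations and ICCs are assumed.

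A reader might infer more than this, in four ways that are not supported:

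- **A fixed 27% and 15%, or a flat threefold error rate.** Those values belong to a correlation of 0.5, no clustering and a z test. The plan specifies clustering terms and Kenward-Roger, under which the error rate is a little over twice nominal.
- **The caregiver mental health hypothesis has no valid test.** It has one, in the unadjusted model. The COPM and PEDI-CAT models are also untouched, since baseline DASS-21 is an ordinary covariate there.
- **The treatment estimate is biased.** Nothing here shows that; the fault lies in the stated precision.
- **All covariates need an interaction with time.** A covariate with the same association at both times is fully handled by a main effect. The protocol does not rule out interactions, and adding them for eight variables with 14 clusters and 84 dyads has a real cost. That is a modelling trade-off, not an error in the plan.

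**What to change.** Add one clause to Additional Analyzes, and carry it into the SAP: when DASS-21 is the outcome, baseline DASS-21 is omitted from the covariate list because the constrained baseline model already uses it; it stays in the list for COPM and PEDI-CAT.

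This loses no information and makes the DASS-21 model one term smaller. The protocol already commits to preparing the SAP and code before 16-week outcomes are collected, so the clause belongs there at that stage.

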### Usual Care Group

The comparison group for this study will receive “Usual Care,” which is known to be highly variable in content and dose across Aotearoa/New Zealand (Widdowson et al., 2015), and internationally (Anaby et al., 2017). Although Usual Care as a control group is problematic (Levack et al., 2019), it remains the best choice in this translational study in which OPC effectiveness is being examined with minimal interruption to other aspects of service delivery.

Prior evaluations of usual care in community paediatric rehabilitation in NZ (Graham et al., 2020; Widdowson et al., 2015) indicate: Goal setting is documented about half of the time; goals seldom address changes in participation in life situations, but rather children's impairments and activities; methods vary from hands on (child) to hands off (talking-based) methods and from child-directed to caregiver-directed; discussion with caregivers during intervention ranges from collaborative to directive and advice-based; provision of advice appears to be a dominant model of practice. Each of these features are deviations from OPC processes. Several strategies are in place to enable the description of what occurs within Usual Care and monitor contamination with the OPC group, including analysis of casenotes (OPC-CA), audio recording and coding of treatment sessions (using the OPC-FM), and collection of dose, location and delivery format of sessions. In addition, the sample size estimate has been set conservatively given the expected variation within the Usual Care group. Data will be collected from each Usual Care therapy session until 16 weeks from the initial session.

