#### OPC-FM

The OPC-FM (Graham & Ziviani, 2021a) is a brief measure of fidelity that distinguishes OPC from expert-led and impairment-oriented approaches and indicates the quality of OPC application. Iterations of the OPC-FM were applied to over 50 recorded OPC sessions, with 10 therapists, by six raters. Formal psychometric testing of the OPC-FM is needed and planned as part of secondary analyzes within this study. The OPC-FM measures the occurrence of behaviour and the quality of this behaviour, with 14 items focusing on therapist behaviour and four items focusing on client responses. A score of 80% or higher is believed to represent high fidelity to OPC.

To monitor fidelity, OPC group therapists will self-administer the OPC-FM following the initial session, and one subsequent self-selected session with each dyad. Experienced OPC trainers will also score the OPC-FM based on audio-recordings of sessions. Therapists will be provided individualized feedback on OPC fidelity and offered additional 1:1 training until fidelity reaches adequate levels, but will not be removed from the primary analysis. Separately, raters, blind to group allocation, will complete the OPC-FM on a random sample of audio recordings from both groups to identify contamination between groups and enable unbiased reporting of treatment delivery.

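### The as-treated sensitivity analysis decides who received OPC from different data in each arm, and partly from client responses, so it loses the protection of randomisation

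*Protocol article*

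**What the plan says.** The main analysis follows allocation: "Participant data will be analyzed as-randomized (intention-to-treat, ITT") (Statistical Methods). Under Additional Analyzes the article adds: "A sensitivity analysis will be conducted on the primary outcome using the as-treated population". A dyad is deemed to have received OPC "if more than half (two out of the three) OPC-FM assessments (researcher-completed or bias-adjusted therapist self-completed") are at 80% or above.

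The OPC-FM section describes the instrument and where its scores come from:

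- Content: the form has items of two kinds, "with 14 items focusing on therapist behaviour and four items focusing on client responses". On the threshold: "A score of 80% or higher is believed to represent high fidelity to OPC".
- Self-completed scores: "OPC group therapists will self-administer the OPC-FM following the initial session, and one subsequent self-selected session with each dyad". No self-completion by Usual Care therapists is described.
- Trainer scores: experienced OPC trainers also rate recordings, in the context of monitoring the OPC therapists and giving them feedback.
- Blinded scores: separate raters "will complete the OPC-FM on a random sample of audio recordings from both groups".

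The Usual Care Group section lists "audio recording and coding of treatment sessions (using the OPC-FM") among the ways of describing usual care and monitoring contamination. It gives no number of coded sessions per dyad.

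**The concern.** An as-treated comparison regroups dyads by what they received. Even at best it is a non-randomised comparison, and two features of this rule weaken it further.

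First, the rule presupposes three assessments per dyad. The data collection described can supply them routinely in the OPC arm (two self-completed forms plus a rating of a recording) but not evidently in Usual Care, where only rated recordings exist. The same degree of OPC-like practice may therefore be classed as treated in one arm and go unrecognised in the other.

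Second, the score includes how the client responded. The primary outcome is a rating of performance on the family's own goals, made mainly by caregivers. A caregiver who engages well in sessions may also report better progress for reasons unrelated to OPC. Selecting on that response can then create a difference where there is none.

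This matters because the design invites contamination. Therapists within one service are allocated to both arms, 20% contamination is budgeted in the sample size, and the Limitations section acknowledges the risk. A reader will look to this analysis for what happens when OPC is actually delivered.

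**Working it through.** The article gives no figure for the as-treated analysis, so there is none to reproduce. Inputs from the article: SD 2 COPM points, a minimal important difference of 2 points, 20% contamination (Sample Size), and 14 + 4 = 18 items with an 80% cut-off (OPC-FM). Assumed here: the proportion p of OPC dyads classed as treated (0.6 to 0.7), the correlation r between the latent fidelity score and outcome (0.2 to 0.4), equal arms, and no clustering.

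**1. Role of the client items.** With equal item weights (an assumption), 80% of 18 is 14.4 points. Perfect therapist items alone give 14/18 = 77.8%, just short. A therapist at 90% on the 14 items has 12.6 points and needs 1.8 of the 4 client points (45%). One at 85% has 11.9 and needs 2.5 (about 63%).

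**2. Availability of scores in Usual Care.** If a fraction f of sessions is coded at random, the chance that a dyad has at least two scores is:

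| Sessions | f = 0.1 | f = 0.3 | f = 0.5 | f = 1.0 |
|---|---|---|---|---|
| 3 | 2.8% | 21.6% | 50% | 100% |
| 6 | 11.4% | 58.0% | 89.1% | 100% |

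The article does not state f.

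**3. No true effect.** Suppose low-fidelity OPC dyads join the comparator and no Usual Care dyad is classed as treated. With z the normal quantile for p and φ the normal density:

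- treated mean = r × 2 × φ(z)/p
- comparator mean = −r × 2 × φ(z)/(2 − p)
- bias = r × 2 × φ(z) × [1/p + 1/(2 − p)]

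For p = 0.6, φ = 0.386 and the bracket is 2.381, so bias = 1.84r. For p = 0.7, φ = 0.348 and the bracket is 2.198, so bias = 1.53r.

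| | r = 0.2 | r = 0.3 | r = 0.4 |
|---|---|---|---|
| p = 0.6 | 0.37 | 0.55 | 0.74 |
| p = 0.7 | 0.31 | 0.46 | 0.61 |

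Against 2 points this is roughly 15 to 37%. If low-fidelity OPC dyads were dropped instead of moved, the bias would be r × 2 × φ(z)/p, about 0.2 to 0.5 points over the same range.

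**4. A true effect of 2, with contamination.** Let c = 0.2 of Usual Care dyads truly receive OPC but go unclassified, with p = 0.7. The comparator mean rises by c × 2/(2 − p) = 0.4/1.3 = 0.31. The estimate is therefore 2 − 0.31 + 1.53r: 1.7 at r = 0, 2.0 at r = 0.2 and 2.2 at r = 0.3 (rounded; simulation gave 1.67, 2.00 and 2.16). The two biases cancel near r = 0.31/1.53 = 0.20.

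**5. Full classification alone is no cure.** In the same simulation with every Usual Care dyad classified, the estimate at r = 0.3 was 0.76 under no effect and 2.77 under an effect of 2. Selection on a prognostic score then operates in both arms.

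**The case against.** The strongest reply has four parts.

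- **It is only a sensitivity analysis.** This stands. The primary analysis is as randomised and keeps low-fidelity therapists. Contamination is also addressed by the sample-size allowance, by case-note audit of study dyads in both arms, and by blinded rating of recordings.
- **Details may be elsewhere.** A reader might infer that most Usual Care dyads cannot be classified. The article does not support that: the sampling fraction is not given, Usual Care sessions are said to be coded, and the chance of two scores runs from 2.8% to 100% in the table above. The full protocol or analysis plan may fix the number. What remains is stated in the article itself: one arm has self-completed scores and the other has none described. The planned bias adjustment of self-scores may correct their level, but it cannot supply scores to Usual Care.
- **The 77.8% figure proves little.** Largely so. It needs equal weights and almost no client credit. With perfect therapist items, 0.4 of 4 client points is enough, and one full client item gives 15/18 = 83.3%. The form scores quality as well as occurrence, and its scoring is not shown. The figure shows that client response can decide classification, not that it usually does.
- **The direction of bias is not fixed.** This also stands. A reader might infer that the analysis always favours OPC. That follows only under no effect with a positive correlation. If OPC works, unrecognised contamination pulls the estimate down.

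**Conclusion.** The point holds as a fault in a rule the article states, not as a complaint about missing detail. Receipt of OPC is established from different sources in the two arms and includes a client response that arises after randomisation, so the as-treated contrast is not protected by randomisation.

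The size depends on assumptions outside the documents. Under no effect, with r of 0.2 to 0.4, 60 to 70% of OPC dyads classed as treated and the rest moved to the comparator, the contrast favours OPC by about 0.3 to 0.7 COPM points. With a true effect of 2 and 20% undetected contamination, it may fall below, at or above the truth. The documents do not determine the net direction.

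Nothing here affects the intention-to-treat result. The risk lies in reading the as-treated figure as confirmation of that result, or as the effect of OPC when properly delivered.

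**What to change.** 1. Define receipt of OPC by one rule in both arms, using only the 14 therapist-behaviour items as scored by the blinded raters. Define it on the sampled recording or recordings, so that the proportion receiving OPC can be estimated in each arm. Sample by dyad, or weight, so that dyads with more sessions do not count more. The 80% threshold was set for the whole form, so the cut-off on the 14 items must be fixed in advance.
2. As the sensitivity analysis for adherence and contamination, report a complier-average estimate: the intention-to-treat difference divided by the between-arm difference in the proportion receiving OPC, with therapist-clustered intervals. For example, with 70% and 20% receiving OPC and an effect of 2 in recipients, the intention-to-treat difference is 1.4 − 0.4 = 1.0, and 1.0/0.5 = 2.0. With no effect the estimate is 0.
3. Label any retained as-treated contrast descriptive.

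The cost is analysis-plan wording, modest programming and possibly a change in how recordings are sampled. Two downsides should be stated. The interval is wider: in the example, dividing by 0.5 doubles it, before allowing for uncertainty in the denominator. The estimate also assumes that allocation acts only through receipt as defined, so partial OPC below the threshold makes it too large. If 70% gain 2 points, 30% gain 1 and no Usual Care dyad receives OPC, the intention-to-treat difference is 1.7 and the estimate is 1.7/0.7 = 2.43. Repeating the calculation at a lower cut-off would show how much this matters.
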